### Interventions

Standard Smoking Cessation Program (SCP): The SCP will consist of group treatment sessions conducted once a week for one hour over a duration of six weeks for each subject. The program is grounded in behavioral therapy principles and will be facilitated by a qualified therapist [53].

Cognitive remediation treatment (CRT): The CRT will be administered as an app-based, chess-focused battery of tasks to be completed twice a week over a period of six weeks, with each session lasting 60 min. The CB-CRT was initially applied as an in-person group training and has since been adapted into a German version compatible with the GYMCHESS^®^ app (https://gymchess.com). This treatment approach utilizes a validated battery aimed at enhancing cognitive functions, including short-term memory, selective and focal attention, pattern recognition, visuospatial abilities, planning skills, and inhibition [54, 55]. In addition to the freely available GYMCHESS^®^ version, the participants will use a modified version with a fixed selection of exercises so that the same cognitive domains will be trained and that training for all participants will take place twice a week. No personal data will be stored during the use of the application. The date and time when the exercises were performed are recorded. Additionally, the number of completed exercises, (in-) correct answers, as well as the difficulty of the task are recorded.

High-intensity interval training (HIIT): This six-week, home-based program consists of four progressive stages, with each session beginning with a 5-minute warm-up and ending with a 3-minute cool-down. The workouts feature high-intensity intervals of 4 min, which are divided into four 1-minute segments of exercise and rest. Each high-intensity interval is followed by 3 min of active rest. Unlike traditional HIIT, this protocol emphasizes high-intensity functional movements that are adaptable to various fitness levels [56]. Low-intensity exercises (walking in place) are performed between high-intensity intervals. In week 1, the participants perform three intervals, each consisting of four sets of 15 s of exercise followed by 15 s of rest. After completing the four sets, there is a 3-minute active rest period. In week 2, a fourth interval is added; see Fig. 3. Weeks 3 and 4 maintain four intervals but modify the exercise/rest ratio to 20 s/10 seconds. Weeks 5 and 6 reduce the active rest to 2 min 30 s. The session durations are 26 min in week 1, 33 min in weeks 2–4, and 31.5 min in weeks 5–6. The participants are required to reach 90% of their maximum heart rate, which was determined during baseline physical exams. The Borg scale [57] is used to assess perceived exertion and ranges from a score between six (no exertion) and 20 (maximal exertion). HIIT sessions are conducted twice weekly, at least three hours before or after sleep, either in the morning or evening. Garmin^®^ (https://www.garmin.com/) fitness trackers and chest straps monitor heart rate, with data collected and visualized through Fitrockr Health Solutions (https://www.fitrockr.com/), a collaborative partner.

**Fig. 3 Fig3:**
[figure not shown]
Training details of high-intensity interval training (HIIT). HR: Heart rate; Borg: Borg Scale to assess perceived exertion

### Baseline Assessment (T1)

After recruitment, screening, and assessment of the inclusion and exclusion criteria, all participants are assigned to one of the four intervention groups and undergo a baseline assessment (T1). This includes obtaining fully informed written consent and conducting a diagnostic interview to validate TUD and any comorbid mental disorders [48]. Additionally, participants must undergo a physical examination to determine their suitability for participating in HIIT and to establish their individual maximum heart rate. The participants are then asked to complete various questionnaires, psychological assessments, and neurophysiological assessments, with an overview of the utilized questionnaires provided in Table 1.

Subsequently, participants undergo approximately one hour of fMRI, which includes two experiments (the N-back task and the stop-signal task (SST)), resting-state fMRI, and anatomical measurements. In addition, the participants undergo polysomnography.

SST: The SST is conducted during fMRI assessment to evaluate response inhibition [58]. The participants are instructed to respond to arrows, indicating left or right directions, by pressing the corresponding key on a remote control held in their hand with the respective thumb. In approximately 20% of the trials, a stop signal represented by an upwards-pointing arrow appears shortly after the presentation of a left or right arrow. The participants are required to withhold their response when the stop signal appears [59]. The task lasts for 13 min and comprises 320 go trials and 80 stop trials, with the aim of achieving an average of 50% stop successes and 50% stop errors. To maintain this balance, the time between the presentation of the go signal (left or right arrow) and the appearance of the stop signal (upwards-pointing arrow) is adjusted dynamically during the experiment. This adjustment, known as the stop signal delay time (SSD), is increased by 50 ms following a successfully inhibited response and decreased by 50 ms after failure. A longer SSD indicates better inhibitory performance. The reaction time and stop-signal reaction time are subsequently computed to estimate response latency in inhibition [60]. Test-retest reliabilities of neural activity during response inhibition were shown to be good [61].

N-back task: To assess working memory capacity, an N-back task with a block design will be conducted during fMRI examination [62]. The participants are required to respond to previously displayed numbers ranging from 1 to 4. In the 0-back condition, participants must press the corresponding key on the remote control for the currently displayed number. In the 2-back condition, participants are instructed to press the button corresponding to the stimulus (numbers 1–4) that appeared two stimuli before the current one. The retest reliability of this task has been shown to be very good [intraclass correlation coefficient of 0.90; 63], and the lack of learning effects during training sessions has been shown to not interfere with exercise outcomes [64].

Resting state: During the final fMRI examination, participants are instructed to fixate their gaze on a cross for an 8-minute resting-state measurement. Research has shown that resting-state measurements can be utilized to predict drug-related responses [65].

fMRI parameters: Scanning will be performed with a 3 T whole-body tomograph (MAGNETOM Prisma; Siemens, Erlangen, Germany). T2*-weighted multiband echo-planar images using a multiband acceleration factor of 6 are acquired in a transverse orientation 20° clockwise to the AC-PC line covering the whole brain with the following parameters: TR = 869 ms, TE = 38 ms, 60 slices, slice thickness = 2.4 mm, voxel size 2.4 × 2.4 × 2.4 mm^3, no interslice gap, field of view = 210 mm, matrix size 88 × 88, acquisition orientation T > C, interleaved slice order, acceleration factor slice = 6, flip angle = 58°, bandwidth = 1832 Hz/Px, prescan normalization, weak raw data filter, LeakBlock kernel, fat sat). The scanner sequences are provided by the Center for Magnetic Resonance Research, University of Minnesota, Minneapolis, MN, USA (https://www.cmrr.umn.edu/multiband/). In addition, a T1-weighted 3D Magnetization Prepared - RApid Gradient Echo dataset consisting of 208 sagittal slices (slice thickness 1 mm, 1 × 1 × 1 mm^3 voxel size, field of view 256 × 256 mm^2, TR = 2000 ms, TE = 2.01 ms, TI = 800 ms, flip angle = 8°) will be acquired. To examine brain iron content, a multiecho GRE imaging sequence will further be acquired (field of view = 220 mm, voxel size 0.9 × 0.9 × 1.4 mm^3, TR = 61 ms, 8 evenly spaced echoes (TE1/TE spacing = 4.5/5.5 ms), bandwidth = 560 (260) Hz/pixel, flip angle = 15°, acquisition time 7:51 min).

Polysomnography (PSG): A CE-certified system (Brain Vision ActiChamp-Plus) will be used to monitor sleep mechanisms. The setup includes 64 scalp electrodes, seven additional electrodes and a breathing belt designed for measuring sleep architecture and characterizing sleep oscillations. The additional electrodes monitor vertical and horizontal eye movements via electrooculography, muscle activity via electromyography, and heart activity via electrocardiography to provide a comprehensive understanding of sleep patterns and to identify/understand abstinence mechanisms during smoking cessation.

Neuropsychological assessments: Multiple neuropsychological assessments will be conducted. The Ravens Progressive Matrices Test [66] is a nonverbal test designed to assess logical thinking through a multiple-choice format. The participants are presented with patterns arranged in matrices and are required to identify the missing piece. The delay discounting task [67] is utilized to measure impulsive decision-making. The Participants make choices between smaller immediate rewards and larger delayed rewards. The Dimensional Card Sorting Task [68] assesses participants’ attentional bias and executive functions by requiring them to match cards to a target card on the basis of a changing rule. The Dot Probe Task [69] evaluates intrinsic attentional selection. Similar to the Dot Probe Task, the Stroop Task [70] measures selective attentional processing by asking participants to name the ink color of words that are incongruent with their meaning. For this study, a three-color Stroop task was implemented (yellow, red, blue), with congruent and incongruent stimuli, letters written in color, and smoking-associated or neutral words written in color. The continuous performance task [71] measures attentional vigilance by requiring participants to respond to specific target stimuli while inhibiting responses to distractors. Finally, the cue reactivity task [72] assesses cue reactivity by presenting participants with blocks of pictures containing either neutral or smoking-related stimuli and measuring craving and smoking desire after each block.

Questionnaires: Please see Table 1 for the questionnaires used throughout the study.

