### Setting

Treatment-seeking participants with TUD according to the fifth version of the Diagnostic and Statistical Manual of Mental Disorders (DSM-5; [48]) will be randomised into four intervention arms. Assessments will take place before (baseline, T1) and after (second investigation day; T2) the six-week smoking cessation program, with a follow-up assessment (T3) three months later. A sport medical examination will be conducted at baseline at an outpatient cardiology clinic, while the other assessments will be conducted at the Central Institute of Mental Health, Mannheim, Germany.

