### Study population and design

The study will be advertised by public advertisements and posters in the local community, newspaper outlets, websites and word of mouth. Interested candidates will undergo a short telephone screen to assess study eligibility and receive information about the study content and organization. A physical examination will then be conducted to ensure that participants are able to perform HIIT. Treatment-seeking smokers (men and women) aged between 18 and 65 years will be included in the study. The inclusion criteria will require prospective participants to meet at least four of the eleven TUD criteria according to the DSM-5, have a body mass index of between 18 and 35, demonstrate sufficient German proficiency to understand questions (both orally and in writing), communicate with investigators, and provide written consent. Additionally, participants must pass a physical examination to ensure that their participation in HIIT is safe. The exclusion criteria will apply to participants with severe somatic or neurological diseases and psychiatric comorbidities other than TUD according to the International Classification of Diseases (ICD-10) and DSM-5. A diagnosis of a sleep disorder (such as restless leg syndrome or insomnia) can also result in exclusion. Additionally, shift workers and night workers will be excluded. Participants will be excluded if they meet any of the following additional criteria: pregnancy and/or breastfeeding; high alcohol intake (screening scores with a score of 4 or higher for women or 5 (or higher) for men [49]); positive drug screening (e.g., amphetamine, benzodiazepine, cocaine, opioids); recent use of psychotropic medications (within the last 14 days, except stable adjusted SSRIs); medications affecting sleep, TUD, or physical activity (e.g., sleep medication, corticosteroids, stimulants); thyroid dysfunction or thyroid stimulation hormone levels outside the normal range; high blood pressure (resting heart rate > 100); or common MRI exclusion criteria (metal and claustrophobia).

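### The protocol is inconsistent on when randomisation occurs: entry criteria are said to be assessed before assignment, yet consent, diagnostic interview and HIIT-fitness check sit in the T1 visit named after it

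*Protocol article*

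**What the plan says.** The only explicit sequence is in Baseline Assessment (T1) of the protocol article. The sentence opens with "After recruitment, screening, and assessment of the inclusion and exclusion criteria" and continues that "all participants are assigned to one of the four intervention groups and undergo a baseline assessment (T1"). The next sentences describe what T1 contains. On consent and diagnosis: "This includes obtaining fully informed written consent and conducting a diagnostic interview to validate TUD and any comorbid mental disorders". On fitness: "participants must undergo a physical examination to determine their suitability for participating in HIIT and to establish their individual maximum heart rate". Questionnaires, neuropsychological tests, fMRI and polysomnography complete the visit.

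Study population and design treats several of these items as conditions of entry. Written consent is an inclusion criterion, and "participants must pass a physical examination to ensure that their participation in HIIT is safe". The exclusions include "psychiatric comorbidities other than TUD according to the International Classification of Diseases (ICD-10) and DSM-5", a positive drug screen and pregnancy. The same section also mentions a physical examination directly after the telephone screen, without placing it relative to randomisation.

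Setting says: "A sport medical examination will be conducted at baseline at an outpatient cardiology clinic". Table 1 marks the structured DSM-5 interview and the sport medical examination at T1 only, and the first drug and pregnancy urine screen at T1.

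**The concern.** The randomised population should consist of people who have consented and are known to be eligible. If assignment precedes T1, anyone who fails the interview, the urine screen or the fitness examination, or who declines consent, leaves after allocation. If the arm has been disclosed by then, leaving can depend on it: CRT adds two 60-minute sessions a week, and a morning or evening slot suits different people. The groups carried forward would then no longer be the groups that were randomised, and the balance from sex-stratified blocks of 8 would be disturbed.

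The T1 measures are also the reference for the change hypotheses, and Statistical analyses compares the six-week outcome with baseline. Self-reported craving, sleep and expectation taken after allocation could be shifted by knowledge of the arm. Analysis cannot reliably undo either problem.

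**Working it through.** **Step 1. Set the sections side by side.**

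| Item | Entry criterion (Study population and design) | Where it is done |
|---|---|---|
| Written consent | Yes | T1 (Baseline Assessment) |
| No other psychiatric comorbidity | Yes | Interview at T1 (Baseline Assessment); T1 only in Table 1 |
| Fit for HIIT | Yes | T1 (Baseline Assessment); at baseline (Setting); sport medical examination T1 only in Table 1; also a physical examination after the telephone screen (Study population and design) |
| Negative drug screen, not pregnant | Yes | First urine screen at T1 (Table 1) |

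If assignment follows the complete assessment of the criteria, all four rows must be finished before assignment. If T1 follows assignment, at least consent is obtained after it. Both cannot hold. No section says that randomisation waits for the end of T1, or that the allocation is withheld during T1.

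**Step 2. Reproduce the planned sample size.** Inputs from Sample size: f = 0.25, alpha 5%, four groups, N = 128, power 80%. For a fixed-effects ANOVA with noncentrality N × f² and N − 4 denominator degrees of freedom:

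- noncentrality = 128 × 0.25² = 8
- numerator df = 1 (a main effect or the interaction in the 2 × 2 layout): power 0.801, which reproduces the plan
- numerator df = 3 (overall test of four groups): power 0.639, which does not

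The df = 1 version is used below.

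**Step 3. The margin.** Three extra per group is 4 × 3 = 12, and 12/140 = 8.6%. Sample size describes it as cover for dropouts only.

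**Step 4. What T1 losses would do.** The loss rates are assumed. It is also assumed that 140 people are assigned and that those lost are not replaced.

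- Left after T1 loss e alone: 140 × (1 − e)
- Left if later dropout also removes 12/140 of the remainder: 140 × (1 − e) × 128/140 = 128 × (1 − e), rounded down
- Number to assign in that case to keep 128: 140/(1 − e), rounded up

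| e (assumed) | Lost at T1 | Left, no later dropout (power) | Left, with later dropout (power) | To assign for 128 |
|---|---|---|---|---|
| 0% | 0 | 140 (0.836) | 128 (0.801) | 140 |
| 5% | 7 | 133 (0.816) | 121 (0.779) | 148 |
| 10% | 14 | 126 (0.795) | 115 (0.757) | 156 |
| 15% | 21 | 119 (0.772) | 108 (0.730) | 165 |
| 20% | 28 | 112 (0.746) | 102 (0.705) | 175 |

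If randomisation comes after these checks, e is zero by construction, and the 12 remain available for dropout during treatment.

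**The case against.** The strongest reply is that the order is loosely drafted rather than wrong. The sentence opens by putting the eligibility assessment before assignment. Study population and design places a physical examination straight after the telephone screen, so the T1 interview may only confirm a diagnosis already made at screening and the T1 examination may mainly set the maximum heart rate. Assignment and T1 are joined by a plain conjunction, not by a word of sequence. Table 1 has no screening column, so screening items could appear only under T1. Fig. 2, the study schedule, is not shown and may place the randomisation step.

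Much of this stands. A reader might infer that exclusions after randomisation are a settled feature of the design and that baseline data are collected with the arm known. The documents do not support either as fact. The opening clause points the other way on the first, and no section says that participants or assessors learn the arm before or during T1. Imaging and polysomnography are also less open to expectation than self-reports. The loss rates above are illustrations. At 10% with no later dropout the shortfall is only 2 of 128, and the lower powers require the dropout margin to be used up as well.

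The reply does not remove the inconsistency. Consent is itself an inclusion criterion and is obtained within T1, so the opening clause cannot be fully true if T1 follows assignment. A telephone screen cannot supply a urine test or a fitness examination. This is also not a matter of an article leaving detail to a fuller document: the sequence is given, and its parts conflict.

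**Conclusion.** The point holds as an internal inconsistency about the time of randomisation. Baseline Assessment (T1) says the criteria are assessed before assignment, then puts consent and checks of those criteria in the visit named after it. If sites follow the text as written, exclusions and refusals would fall after allocation, and baseline measures would be taken after allocation with nothing said about withholding it.

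The size cannot be derived from the documents. What is fixed is the margin, 12 of 140 (8.6%), which such losses would share with ordinary dropout; the Discussion itself names high dropout as a potential limitation. A T1 loss of 10% to 20%, purely as an assumption, would be 14 to 28 people. Power would be 0.795 to 0.746 from that loss alone, or 0.757 to 0.705 if the dropout margin is also used, against the planned 0.80. The bias from losses that depend on the arm, or from baselines shifted by knowing it, is conditional on early disclosure and is not quantified here.

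**What to change.** Reconcile Setting, Study population and design, Baseline Assessment (T1) and Table 1, and state one order:

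1. written consent;
2. all eligibility checks (diagnostic interview, urine screens, sport medical examination);
3. all T1 questionnaires, neuropsychological tests, fMRI and polysomnography;
4. randomisation and disclosure of the arm, as the last step before the intervention starts.

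If a physical examination before T1 is separate from the sport medical examination, say so and give it its own place in Table 1. A screening column and a randomisation row would make the sequence plain.

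The cost is protocol wording and the timing of one step. No procedure is added. Participants learn their arm and time slot somewhat later, so scheduling has less lead time. People who fail a check are then screening failures and do not use the dropout margin.

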### Second investigation day (T2)

The second investigation day (T2) is conducted after the completion of the 6-week SCP. Similar to T1, participants are asked to complete different fMRI assessments, as well as neuropsychological assessments and questionnaires. A second PSG will also take place. A complete list of all the measurements is provided in Table 1.

### Follow-up (T3)

Three months after the second investigation (T2), the participants will receive the same self-rating questionnaires as for T1 and T2, see Table 1. Abstinence or relapse as well as nicotine consumption will be assessed during a final telephone interview. In addition, between T2 and T3, biweekly telephone interviews will take place to assess abstinence or relapse during the follow-up period of 90 days.

**Table 1 Tab1:** Measurements and interventions

		T1	T2	I1-6	FU1-5	T3
**Baseline information and medical screening**	Sociodemographic data	x	(x)^*^			(x)^*^
	Internistic, neurological examination	x	(x)^*^			(x)^*^
	Drug/pregnancy urine screening	x	x			
	Menstrual cycle	x	x			
	Body Mass Index	x	x			x
	Carbon monoxide	x	x	x		
	Structured Clinical Interview for DSM-5	x				
	Sport medical examination	x				
	Edinburgh Handedness Inventory (73)	x				
**Questionnaires Smoking**	Questionnaire of Smoking Urges (74)	x	x			x
	Fagerstrøm Test of Cigarette Dependence (75)	x	x			x
	Craving Automated Scale for Cigarette (CAS-CS;	x	x			x
	adapted from CAS-A,(76))					
	Smoking Consequences Questionnaire (SCQ,(77))	x	x			x
	Wisconsin Smoking Withdrawal Scale (WSWS,(78))	x	x			x
	Cigarette Craving (Visual Analogue Scale)			x		
**Questionnaires Clinic**	Center for Epidemiological Studies Depression Scale (CES-D/ADS,(79))	x	x			x
	Perceived Stress Scale (PSS,(80))	x	x			x
	State-Trait-Anxiety Inventory (STAI,(81))	x	x			x
	PANAS Trait/State (82)	x	x			
	Barratt Impulsiveness Scale (BIS,(83))	x	x			x
	Creature of Habit Scale (COHS,(84))	x	x			x
	ASRS-V1.1 Screener (WHO, 2004)	x				
**Questionnaires Sleep**	Caffeine consumption questionnaire - revised	x	x			x
	(CCQ, (85))					
	Pittsburgh Sleep Quality Index (PSQI,(86))	x	x			x
	Global physical activity questionnaire (GPAQ, WHO)	x	x			x
	Munich Chronotype Questionnaire (MCTQ,(87))	x	x			x
	Stanford Sleepiness Scale (SSS,(88))	x	x			x
	Saint Mary's Hospital Sleep Questionnaire (89)	x	x			x
	Sleep Problems			x		
**Questionnaires Therapy expectation**	Goal Attainment scaling (90)	x	x			x
**Outcome consumption**	Form 90 interview (91)	x	x		x	x
	Time to relapse	x	x		x	x
	Days of abstinence	x	x	x	x	x
	Number of cigarettes	x	x	x	x	x
**Neuropsychological Assessment**	Delay Reward Discounting Task (67)	x	x			
	Dimensional Card Sorting Task (68)	x	x			
	Dot-probe (69)	x	x			
	Raven’s Progressive Matrices Test (66)	x				
	Cue reactivity (modified after (92)	x	x			
	(Nicotine) Stroop Task (modified after (70))	x	x			
	Continuous Performance Task (93)	x	x			
	Psychomotor Vigilance Task (94)	x	x			
**Functional magnetic resonance imaging**	Structural MRT	x	x			
	Resting state	x	x			
	mGRE	x	x			
	N-Back Task (62)	x	x			
	Stop-Signal Task (60)	x	x			
**Polysomnography**	Electroencephalography	x	x			
**Interventions**	Standard SCP plus CRT + HIIT			X		
	Standard SCP plus HIIT			x		
	Motivation and difficulty (HIIT, SCP) Visual Analogue Scale			x^**^		
	Borg Scale (57)			x^***^		
	Evaluation of each intervention (HIIT, CRT, SCP)					
	Visual Analogue Scale					

Note: T1 = first investigation day, T2 = second investigation day, I = Intervention (weeks 1 to 6), FU = biweekly follow-up period, T3 = final investigation day after three months, mGRE = multiecho GRE sequence, SCP = smoking cessation program, HIIT = high-intensity interval training. *updated if necessary. ** Motivation and difficulty of the intervention will be assessed after each intervention time point. ***Evaluation of all three interventions will be assessed weekly (‘does the intervention seem logical to you’, ‘how promising does the intervention appear to you’, ‘how likely would you recommend the intervention to a friend’, ‘how interested are you in participating in the training’, ‘how successful do you think the training will be’)

